#### Primary analysis

A summary of objectives, outcomes, and analyses is presented in Table 3. We will report feasibility outcomes descriptively by site as proportions with 95% CIs. We will also report whether each feasibility outcome met the criteria for feasibility success.

**Table 3 Tab3:** Summary of objectives, outcomes, success criteria, and analyses

Primary			
Objective	Outcome	Success criteria	Analysis
Feasibility	Recruitment	Each site should recruit 50 participants in 12 months or less	Descriptive—proportions with 95% CI
	Adherence to visit windows	At least 75% of study visits should be within the defined windows	
	Participant retention	Loss to follow-up should remain under 15%	
	Data completeness	Questionnaire completion rates should remain over 80%	
Secondary			
Objective	Outcome	Analysis	
Determine how a history of IPV affects injury-related complications	Injury-related complications	Proportions of patients experiencing injury-related complications by group with 95% CI; logistic regression.	
Determine how a history of IPV affects return to pre-injury function	Return to pre-injury function	Proportion of patients achieving return to pre-injury level of function in each group at baseline, 3 months, 6 months, and 12 months with 95% CI; logistic regression.	
Determine incident cases of IPV	New IPV disclosures	Incidence statistic with 95% CI.	
Determine how a history of IPV affects health care and support service use	Utilization and associated costs of support services and hospitalizations	Proportions of women using each service per group over 12 months, median number of times that participants used each service with IQR. Estimated mean costs with 95% CI in each group and bootstrap differences between those with a history of IPV and those without with 95% CI.	
Determine how patterns of IPV change over time	Changes in abuse severity/frequency and type	Proportion of patients who experienced no abuse, a stable level of abuse, escalating abuse, and de-escalating abuse over 12 months with 95% CI; graphically.	
Determine how a history of IPV affects HRQL after a musculoskeletal injury	EuroQuol-5 Dimensions (EQ-5D)	Mean change in HRQL from baseline to the 3 month, 6 month, and 12 month visits, by group with 95% CI.	
Determine how abused women’s stage of change changes over time	Domestic Violence Survivor Assessment (DVSA)	Change in stage of change from baseline at 3 months, 6 months, 9 months, and 12 months.	

*CI* confidence interval, *IQR* interquartile range, *HRQL* health-related quality of life

#### Secondary analyses

The analyses of clinical outcomes will be exploratory in nature since the primary focus is on assessing feasibility. We will therefore not present *p* values for comparative analyses. We will not carry out any imputation for missing data in this pilot study.Injury-related complications—We will present proportions of patients experiencing injury-related complications in each group (i.e. women with and without a history of IPV) over 12 months with 95% CI. We will also perform an exploratory logistic regression analysis.Return to pre-injury function—We will report the proportion of patients achieving return to pre-injury level of function in each group at baseline, 3 , 6 , and 12 months with 95% CI. We will also perform an exploratory logistic regression analysis.New IPV disclosure*—*New IPV disclosures will be reported as an incidence statistic with 95% CI.Utilization and costs of health, legal, and social support services—Will be reported descriptively as proportions of women using each service per group over 12 months as well as the median number of times that participants used each service with interquartile range (IQR). Direct costs will be derived by assigning costs to adjudicated injury-related complications and self-reported utilization of health care services based on provincial case costing registries and health care provider schedule of benefits. All remaining direct costs will be estimated by multiplying self-reported units of utilizations (e.g. visits to social worker, use of mental health services) by an estimate of the cost per unit of service based on provincial or national average charges. Indirect costs will be calculated using self-reported annual income and return to function. Costs will be presented as means with 95% CIs, and histograms. Due to the non-normality of cost data, non-parametric bootstrap estimates will be used to present the difference in mean costs between those with and without a history of IPV. Multivariable sensitivity analysis will be conducted by using 95% CI and reported cost ranges for input parameters. All costs will be inflated to 2018 Canadian dollars using the appropriate price indices.Changes in IPV type and severity—We will report the proportion of patients who experienced no abuse over 12 months, a stable level of abuse over 12 months, escalating abuse, and de-escalating abuse over 12 months with 95% CI. We will present this graphically.Health-related quality of life—We will report the mean change in HRQL from baseline to the 3-, 6-, and 12-month visits by group with 95% CI. We will also estimate utility, which will be modelled over the course of 1-year follow-up, using 3-, 6-, and 12-month EQ-5D scores and standard trapezoidal rules. Utility will be presented as quality adjusted life years (QALYs) for each group, with 95% CI, where 1 represents full health and 0 represents death. The difference between each group will be presented as QALYs lost.Stages of change—We will report the change in stage of change from baseline at 3, 6, 9, and 12 months for patients who report that their current relationship is or was abusive.

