#### Clinical objectives

Clinical objectives in this pilot study are exploratory. The clinical objectives of the PRAISE-2 study include determining (1) how a history of IPV affects injury-related complications; (2) how a history of IPV affects return to pre-injury function; (3) incident cases of IPV after a musculoskeletal injury if the injury was not the result of IPV; (4) how a history of IPV affects health care and support service use after a musculoskeletal injury; (5) how a history of IPV affects health-related quality of life after a musculoskeletal injury; (6) how patterns of IPV change over time after a musculoskeletal injury; and (7) how abused women’s stage of change (i.e. readiness to make changes to move toward a life free from violence) changes over time after a musculoskeletal injury.

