### Patient selection

#### Eligibility criteria

We will use broad eligibility criteria to increase the generalizability of the study. The inclusion criteria are (1) adult females (at least 16 or 18 years of age depending on local ethics requirements); (2) patients presenting to participating fracture clinics within 6 weeks of their injury; and (3) patients presenting with a fracture or dislocation which is being managed with either surgical or non-surgical treatment.

The exclusion criteria are (1) unwilling to or unable to provide consent; (2) unable to complete the study questionnaires in a private location, due to safety and confidentiality; (3) unwilling or unable to follow the study protocol or their attending surgeon has concerns about their ability or willingness to follow study protocols; and (4) does not speak and write in English or the dominant language of the local clinic. Due to the sensitive nature of the topic, only patients who can consent for themselves will be considered for participation.

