### Study outcomes

#### Primary (feasibility) outcomes

The primary outcome of the pilot study is feasibility including recruitment, adherence to visit windows, participant retention, and data completeness. The criteria for success of feasibility are as follows:Recruitment—Our recruitment strategy will be considered feasible if each site is able to recruit 50 participants in 12 months or less after their training call/visit.Adherence to visit windows—We have attempted to align study visit windows with clinical standard of care visits; however, standard of care visits can vary by region and/or type of injury. We expect that at least 75% of study visits should be within the defined windows in Table 1.Participant retention—While 20% loss to follow-up has traditionally been considered the industry standard [26], there is evidence from orthopaedic studies that bias begins to affect study results at even lower rates of loss to follow-up [27]. Therefore, our loss to follow-up minimization strategy will be considered feasible if loss to follow-up remains under 15%.Data completeness—Based on our experience in previous multicentre orthopaedic trauma studies, we are typically able to obtain questionnaire completeness rates of 75–85% at 12 months. Therefore, we will consider our data collection strategies to be feasible if questionnaire completion remains over 80%.

**Table 1 Tab1:** PRAISE-2 schedule of events

Assessment	Baseline (0–6 weeks from injury)	1 month (2–6 weeks from injury)	3 months (11–15 weeks from injury)	6 months (24–28 weeks from injury)	12 months (48–56 weeks from injury)
Target visit window					
Screening form	X				
Informed consent	X				
Demographic characteristics form	X				
Injury characteristics form	X				
IPV status (type, frequency, severity)	X	X	X	X	X
Assessment for complications	X	X	X	X	X
Support service utilization	X	X	X	X	X
Return to function	X	X	X	X	X
EQ-5D	X	X	X	X	X
Stages of change	X	X	X	X	X
Radiograph	(X)	(X)	(X)	(X)	(X)
Clinic notes	(X)	(X)	(X)	(X)	(X)

(X) = Only if required to adjudicate an adverse event

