### Study follow-up

Participants will complete the questionnaires in the surgical clinic (baseline), and at 1, 3, 6, and 12 months after the baseline assessment. Participants will be provided with the option of completing the study questionnaire in the clinic or over the telephone (Fig. 1). Table 1 lists the assessments at each study time point. We chose a 12-month follow-up period because this is the most common follow-up length in other IPV studies [34].

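### Table 3 answers the HRQL objective only with change from a post-injury baseline of variable timing, which removes any IPV-related deficit already present at that visit

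*Protocol article*

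**What the plan says.** The fifth clinical objective is to determine "how a history of IPV affects health-related quality of life after a musculoskeletal injury". The groups, as defined under Secondary analyses, are "women with and without a history of IPV".

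The analysis appears twice. Secondary analyses says "We will report the mean change in HRQL from baseline to the 3-, 6-, and 12-month visits by group with 95% CI". The HRQL row of Table 3 says "Mean change in HRQL from baseline to the 3 month, 6 month, and 12 month visits, by group with 95% CI" and lists no other analysis.

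Baseline is the first study visit. Its column in Table 1 is headed "Baseline (0–6 weeks from injury", which matches the inclusion criterion of "patients presenting to participating fracture clinics within 6 weeks of their injury". The 1-month window in Table 1 is 2–6 weeks from injury and lies wholly inside the baseline window.

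In the same paragraph, Secondary analyses also plans QALYs per group with a 95% CI, built by the trapezoidal rule from the EQ-5D at 3, 6 and 12 months, and a difference between the groups. All clinical analyses are described as exploratory, and no p values are to be shown for comparisons.

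**The concern.** The objective concerns HRQL after injury in women with and without a history of IPV. That history and the injury both come before the first EQ-5D, so the baseline score is itself a post-injury outcome that IPV may already have affected. The Background says that IPV victims experience more physical and mental health problems, so a deficit at the first visit is plausible on the protocol's own premise. Subtracting that score removes the deficit.

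The change also depends on where in early recovery each woman was enrolled. One woman's baseline can fall at the same time after injury as another's 1-month visit.

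At stake is how the pilot's HRQL result will be read. A difference in change near zero could be taken to mean that HRQL does not differ by IPV history when it does. The estimates will be published with confidence intervals, and the protocol intends pilot data to inform the definitive sample size calculation, although it does not say that HRQL will be used for this.

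**Working it through.** The protocol gives no target difference, SD or precision for HRQL, so there is no figure to reproduce. The check is algebra plus an illustration on assumed curves.

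**1. Change score.** Let D(t) be the mean EQ-5D with a history of IPV minus the mean without, at time t. The difference in mean change is D(t) − D(0).
- Constant deficit d: (−d) − (−d) = 0, for any d and at every visit.
- Deficit growing from 0.05 at baseline to 0.10 at 12 months: (−0.10) − (−0.05) = −0.05. Only the part equal to the baseline gap is removed.

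**2. QALY difference as worded.** The trapezoid over the 3-, 6- and 12-month scores spans 0.25 + 0.50 = 0.75 year and does not use the baseline score. A constant deficit of 0.05 gives 0.75 × 0.05 = 0.0375 QALY lost; 0.10 gives 0.75 × 0.10 = 0.075.

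**3. Timing, with no IPV effect.** The assumed recovery is u(t) = 0.8 − 0.4·exp(−t/τ), with t in weeks from injury and τ = 4, 8 or 12. One group is assumed to have its baseline at week 4 and the other at week 2. None of these values is in the protocol.

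With visits counted from injury, the difference in change at every visit is u(2) − u(4) = −0.4·[exp(−2/τ) − exp(−4/τ)]:
- τ = 4: −0.4 × (0.6065 − 0.3679) = −0.095
- τ = 8: −0.4 × (0.7788 − 0.6065) = −0.069
- τ = 12: −0.4 × (0.8465 − 0.7165) = −0.052

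The level and QALY differences are 0. As a simpler check, an assumed linear gain of 0.02 to 0.04 per week over 2 weeks gives 0.04 to 0.08.

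**4. The other visit clock.** Table 1 counts from injury ("3 months (11–15 weeks from injury"), but Study follow-up places visits "and at 1, 3, 6, and 12 months after the baseline assessment". These statements need to be reconciled, so step 3 was repeated on the second clock. At 3 months, taken as 13 weeks after baseline, the level difference is u(17) − u(15) = 0.004, 0.014 or 0.018 for τ = 4, 8 or 12. Subtracting the baseline difference leaves a difference in change of −0.092, −0.055 or −0.034. The QALY difference is at most 0.005.

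| Assumed situation | Difference in change | Difference in level | Difference in QALYs |
|---|---|---|---|
| Constant deficit 0.05 | 0 | −0.05 | −0.0375 |
| Constant deficit 0.10 | 0 | −0.10 | −0.075 |
| No effect, 2-week gap, visits from injury | −0.052 to −0.095 | 0 | 0 |
| No effect, 2-week gap, visits from baseline (change and level at 3 months) | −0.034 to −0.092 | 0.004 to 0.018 | at most 0.005 |

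**The case against.** The strongest reply is the QALY analysis. It is in the same paragraph, it uses follow-up levels without subtracting baseline, and it is the only HRQL summary for which the text expressly promises a difference between groups. A reader might infer from Table 3 that the study cannot answer the HRQL objective, or that the IPV effect is lost altogether. The documents do not support that: the QALY difference keeps a persistent deficit and barely responds to baseline timing, and the change score itself still shows any later divergence.

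A reader might also infer that the change comparison is in fact biased by late presentation. That is not supported either. No section says that women with a history of IPV present later, and all new female patients within 6 weeks of injury are screened.

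Further, change from the first assessment is a legitimate description of recovery, the analysis is exploratory, and an article may leave tabulation by visit to a fuller plan.

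Most of this stands and limits the point. What remains is what the article does fix. It ties the objective to change alone in Table 3, leaves the QALY difference out of that table, and gives no rule for reading the two when they disagree. The QALY figure is also one aggregate, which shows neither the level at each visit nor the early post-injury level.

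**Conclusion.** The point holds for the change-from-baseline summary. It discards any group difference already present 0–6 weeks after injury; that is algebra and needs no assumption. For constant deficits of 0.05 to 0.10, the two planned summaries would disagree: 0 on change, against 0.0375 to 0.075 QALY lost.

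The timing effect is conditional. It requires presentation time to differ by IPV history, and its size (about 0.05 to 0.10 for a 2-week gap, visits counted from injury) rests on assumed recovery curves.

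A comparison of levels would include differences that predate the injury, but a baseline taken after injury cannot separate these from early post-injury effects. The consequence is limited to interpretation of one exploratory outcome; no feasibility criterion depends on it. It is worth correcting because the correction costs almost nothing.

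**What to change.** In the HRQL paragraph of Secondary analyses and the HRQL row of Table 3:

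- Make the main summaries the mean EQ-5D level by group at 3, 6 and 12 months with 95% CI, and the between-group QALY difference. Show the baseline level as a post-injury outcome.
- Keep mean change from baseline as a secondary description of recovery.
- Report days from injury to the baseline assessment by group, or adjust for them, wherever the baseline score is used.

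The cost is a sentence or two of text and one table row, with slightly more reporting in an exploratory analysis. The EQ-5D is already scheduled at every visit, so no new data item is needed.

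### The EQ-5D scores listed for the one-year QALY (3, 6 and 12 months) span only nine months; the baseline and 1-month scores are collected but not named

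*Protocol article*

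**What the plan says.** The quality-of-life item under Secondary analyses gives two analyses of the EQ-5D. The first is a change score: "We will report the mean change in HRQL from baseline to the 3-, 6-, and 12-month visits by group with 95% CI". The second is the QALY. Utility is to be "modelled over the course of 1-year follow-up", obtained "using 3-, 6-, and 12-month EQ-5D scores and standard trapezoidal rules", on a scale "where 1 represents full health and 0 represents death". The group comparison follows: "The difference between each group will be presented as QALYs lost".

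The collection schedule is wider than the list of scores used. Table 1 marks the EQ-5D at baseline, 1, 3, 6 and 12 months, and Study follow-up agrees: "Participants will complete the questionnaires in the surgical clinic (baseline), and at 1, 3, 6, and 12 months after the baseline assessment". On missing data, Secondary analyses says: "We will not carry out any imputation for missing data in this pilot study". Nowhere does the article add the baseline or 1-month score to the QALY, carry the 3-month score back to the start, or rescale a nine-month area to a year.

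**The concern.** A trapezoidal area needs a value at each end of the period that it covers. The first listed score is at 3 months, so the area starts there and the first quarter of the stated year has no defined contribution. Whoever runs the analysis must drop that quarter, fill it, rescale, or assume that baseline was intended, and these choices give different answers.

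The quarter left out comes just after a fracture or dislocation. Utility can reasonably be expected to be low then and to change quickly, although the article gives no utilities. An early difference between the groups would fall in exactly this period. The reported result is the between-group difference, so a gap in the definition passes straight into it and could be carried into the definitive study that the pilot is meant to inform.

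**Working it through.** The article states no QALY value, so there is no figure to reproduce. The one internal check is its anchor of 1 for full health.

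**Inputs.** Listed times 3, 6 and 12 months (Secondary analyses); collected times 0, 1, 3, 6 and 12 months (Table 1, Study follow-up). Utilities are assumed for illustration: 0.40, 0.55, 0.70, 0.80 and 0.85 at the five times. Nominal visit times are used, with baseline at time 0.

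**Formula.** QALY = sum over adjacent visits of (time gap in months / 12) × (mean of the two utilities). This is a weighted sum of the scores, with these weights in years:

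- All five scores: 1/24, 3/24, 5/24, 9/24, 6/24; total 24/24 = 1.00.
- Listed scores only (3, 6, 12 months): 3/24, 9/24, 6/24; total 18/24 = 0.75.
- Baseline read in (0, 3, 6, 12 months): 3/24, 6/24, 9/24, 6/24; total 1.00.

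**Assumed path.**

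- All five: (0.40 + 3×0.55 + 5×0.70 + 9×0.80 + 6×0.85)/24 = 17.85/24 = 0.7438.
- Listed only: (3×0.70 + 9×0.80 + 6×0.85)/24 = 14.40/24 = 0.600.
- 3-month score carried back: 0.600 + 0.25×0.70 = 0.775.
- Rescaled to a year: 0.600/0.75 = 0.800.
- Baseline read in: (3×0.40 + 6×0.70 + 9×0.80 + 6×0.85)/24 = 17.70/24 = 0.7375.

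**Group differences.** A gap of 0.10 is multiplied by the total weight of the visits at which it is present. With all five scores, a gap at baseline and 1 month only is worth 0.10 × (1 + 3)/24 = 0.017. A gap from month 3 on is worth 0.10 × (5 + 9 + 6)/24 = 0.083.

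| Treatment of months 0 to 3 | Constant full health | Assumed path | Gap 0.10 throughout | Gap 0.10 at 0 and 1 month only | Gap 0.10 from month 3 on |
|---|---|---|---|---|---|
| All five scores | 1.00 | 0.7438 | 0.100 | 0.017 | 0.083 |
| Dropped (literal) | 0.75 | 0.600 | 0.075 | 0.000 | 0.075 |
| 3-month score carried back | 1.00 | 0.775 | 0.100 | 0.000 | 0.100 |
| Rescaled by 0.75 | 1.00 | 0.800 | 0.100 | 0.000 | 0.100 |
| Baseline read in | 1.00 | 0.7375 | 0.100 | 0.0125 | 0.0875 |

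Only the literal reading breaks the article's own anchor and shrinks a constant gap (0.075 against 0.100, or 25%). Carrying back and rescaling repair both, but they still give an early-only gap no weight, and they overstate a gap that starts at 3 months (0.100 against 0.083). Reading baseline in comes closest to the five-score result.

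**The case against.** The strongest reply is that baseline is implied. The preceding sentence uses it as the reference for the change scores, the QALY sentence refers to a full year, and a standard trapezoidal calculation needs a starting value. On that reading the assumed path is off by 0.7438 − 0.7375 = 0.006, under 1%, and the fault is mainly one of wording. This is a fair possibility but remains an inference: the same section names baseline where it is used, for return to function and for HRQL change, and omits it here.

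The 1-month visit is also absent from the return-to-function and HRQL-change analyses, although both measures are collected then. Leaving it out of the QALY is therefore consistent with the rest of the plan; adding it is an improvement, whereas the missing start of the interval is the defect.

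The consequences are limited too. The clinical analyses are exploratory and without p values, QALYs do not appear in Table 3, and no cost-effectiveness ratio is mentioned. With 250 women and 1 in 3 having a lifetime history of IPV, the groups are about 83 and 167. For an assumed QALY standard deviation of 0.15 to 0.25, the 95% CI half-width is 1.96 × SD × √(1/83 + 1/167), about 0.04 to 0.07 before attrition. An early-only effect of 0.017 lies well inside that. This stands, and it bears on severity; it does not make the listed inputs sufficient for a one-year QALY.

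A reader might go further and infer that every participant's QALY will be wrong and the group difference 25% too small. The article does not support that. Both claims require months 0 to 3 to be dropped with no filling or rescaling. Under carry-back, a woman whose utility is stable up to 3 months gets the right value and a constant difference is reported in full.

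**Conclusion.** The point holds as a defect of specification. The listed scores cover 9 of the 12 months, and the article states no rule for the other three. The size depends on what the analyst does:

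- **Dropped:** constant full health gives 0.75, and a constant difference is 25% too small.
- **Filled from 3 months, or rescaled:** a constant difference is right, but an early one that has gone by 3 months is missed (0.017 QALY for 0.10 at baseline and 1 month).
- **Baseline implied:** the error is small, 0.006 on the assumed path.

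The 0.75 total and the 25% follow from the visit times alone. The path values rest on assumed utilities, and all figures use nominal visit times. Recruitment, visit adherence, retention, data completeness and the sample size are untouched. The scores are collected in any case, so nothing is lost if the rule is corrected before analysis. It merits a moderate correction.

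**What to change.** In the QALY sentence, replace the list of time points with: baseline, 1-, 3-, 6- and 12-month EQ-5D scores.

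Add that the trapezoids use each woman's actual assessment dates, and state whether time runs from injury or from the baseline assessment. This is needed because Table 1 counts its windows from injury and lets baseline (0 to 6 weeks) overlap the 1-month visit (2 to 6 weeks), while Study follow-up counts visits from baseline. If injury is the origin, a woman enrolled at 5 or 6 weeks has unobserved early weeks, and the text should say how they are treated.

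The cost is one or two sentences, with no new data and no change to the visit schedule. A repeated-measures model that yields the area from all five visits would be an option for women who miss a questionnaire. That is a separate choice and not part of this correction.

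### The cost and QALY contrasts between women with and without a history of IPV are described without covariate adjustment, and the QALY difference carries the causal label QALYs lost

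*Protocol article*

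**What the plan says.** All of this is in the Protocol article.

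- **Objectives.** Clinical objectives includes "how a history of IPV affects health-related quality of life after a musculoskeletal injury", and Table 3 repeats it as "Determine how a history of IPV affects HRQL after a musculoskeletal injury". The objective on health care and support service use also asks how a history of IPV *affects* the outcome.
- **Costs (Secondary analyses).** "non-parametric bootstrap estimates will be used to present the difference in mean costs between those with and without a history of IPV". No covariate is named.
- **Cost sensitivity analysis.** "Multivariable sensitivity analysis will be conducted by using 95% CI and reported cost ranges for input parameters". This varies the cost inputs. It does not adjust for differences between the women in the two groups.
- **QALYs.** Utility is modelled "using 3-, 6-, and 12-month EQ-5D scores and standard trapezoidal rules", QALYs are given for each group with a 95% CI, and then: "The difference between each group will be presented as QALYs lost".
- **EQ-5D change.** "We will report the mean change in HRQL from baseline to the 3-, 6-, and 12-month visits by group with 95% CI". No between-group difference is stated here.
- **Regression.** For complications and for return to function only: "We will also perform an exploratory logistic regression analysis". Its covariates are not listed.
- **Status.** All clinical analyses are exploratory, with no p values and no imputation.

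**The concern.** The comparison is observational. Every consenting eligible woman is followed and is classified by the IPV history that she reports. Eligibility is broad by design: adult women with any fracture or dislocation, treated surgically or not, at sites in Canada, the Netherlands, Spain and Finland. The two groups may therefore differ in age, country and injury for reasons unrelated to IPV, and each of these can move both EQ-5D and cost. Costs have one further route: indirect costs are computed from self-reported annual income and return to function, so any income difference between the groups enters the cost contrast by construction.

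Followed as written, the plan gives a difference in group means for costs and for QALYs. It then names the QALY difference as a loss, under an objective worded as an effect of IPV. The Background says that evidence of a direct effect of IPV on outcomes is needed to change surgeons' practice, so readers are likely to take the label causally. At stake is how an exploratory result will be read. The feasibility conclusions are not affected.

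**Working it through.** **1. What the text assigns to each outcome (Secondary analyses and Table 3)**

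| Outcome | Between-group contrast stated | Regression named | Label |
|---|---|---|---|
| Complications | Proportions by group | Logistic | Neutral |
| Return to function | Proportions by group | Logistic | Neutral |
| Costs | Bootstrap difference in means | None | Neutral |
| EQ-5D change | None; means by group only | None | Neutral |
| QALYs | Difference between groups | None | QALYs lost |

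The concern therefore covers two stated contrasts (costs and QALYs) and one label (QALYs only).

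**2. Whether baseline data for adjustment exist**

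Table 1 schedules a demographic form and an injury form at baseline. Site is known, since feasibility is reported by site. Age is not named as a field. That it is recorded is an inference from the demographic form and the age criterion for eligibility.

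**3. Precision of an unadjusted difference**

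The plan gives no figure to reproduce. Inputs from Sample size determination: 250 women, about 10% loss, 1 in 3 with lifetime IPV, 1 in 6 with IPV in the past year.

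- Retained: 250 × 0.90 = 225.
- Lifetime IPV: 225/3 = 75 with and 150 without. Half-width = 1.96 × SD × √(1/75 + 1/150) = 0.277 SD.
- At an assumed QALY SD of 0.15, 0.20 or 0.25: 0.042, 0.055 or 0.069.
- Past-year IPV: 225/6 = 37.5 with and 187.5 without. Half-width = 1.96 × SD × √(1/37.5 + 1/187.5) = 0.351 SD, or 0.053 to 0.070 at an SD of 0.15 to 0.20.

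These treat every retained woman as having complete EQ-5D data. With no imputation, the real intervals would be wider.

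**4. Possible size of confounding (illustration; every input here is an assumption)**

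Bias ≈ group difference in the covariate × effect of the covariate on QALYs.

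- Age gap of 5 to 15 years at 0.001 to 0.005 QALY per year: 5 × 0.001 = 0.005 up to 15 × 0.005 = 0.075.
- A middle case, 10 years at 0.002 to 0.004: 0.02 to 0.04. Against half-widths of 0.042 to 0.055, this is 0.02/0.055 = 36% up to 0.04/0.042 = about 95%.
- Injury-mix difference of 10 to 20 percentage points with an effect of 0.05 to 0.10: 0.10 × 0.05 = 0.005 up to 0.20 × 0.10 = 0.02.

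The bias could be negligible or about as large as the sampling error; only the extreme age corner exceeds it. The document holds nothing that would narrow this range or fix the sign.

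**5. Weeks from injury to baseline**

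Baseline may fall 0 to 6 weeks after injury. The planned QALY uses only the 3-, 6- and 12-month scores, and Table 1 sets those windows in weeks from injury, so on that schedule the timing of baseline does not enter the QALY. (Study follow-up counts visits from baseline instead, which is a separate mismatch.) Baseline timing does affect EQ-5D change from baseline, and matters there if the two groups' changes are compared.

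**The case against.** The strongest reply is that an article commonly leaves covariate lists and model form to an analysis plan. The text never says that the contrasts will be unadjusted, and a bootstrap describes how uncertainty is obtained without excluding adjustment. The logistic regressions name no covariates either, so they are not shown to be adjusted. The clinical analyses are exploratory and carry no p values. Much of this stands, and the absence of a covariate list alone would not be a finding. But the article does say which outcomes receive a regression, does state the cost and QALY contrasts, and does fix the label. An unseen analysis plan would not remove that label from the published text.

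A second reply concerns the remedy. Sample size determination notes that 1 in 50 women present because of an IPV-related injury, so adjusting for injury type or treatment may remove part of an IPV effect. About 75 exposed women and skewed costs also limit how many covariates a model can carry. Both points are sound and shape the fix.

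A reader might also infer more than the documents support:

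- That the groups are self-selected. They are classified by reported exposure among all consenting women; non-randomised is the accurate word.
- That costs or EQ-5D change are also reported as losses. The label is attached to QALYs alone.
- That a biased cost or QALY difference would drive the definitive study. The document says that pilot data will inform its sample size and names injury-related complications as its subject. It gives cost and QALY differences no such role.

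**Conclusion.** The point holds for the cost and QALY contrasts and for the QALY label. As described, these are comparisons of non-randomised groups with no adjustment named, and the QALY difference is worded as a loss due to IPV. It does not hold as a claim of known bias. The half-width of about 0.28 SD rests on the plan's own 250 women, 10% loss and 1 in 3 exposed, and its QALY values on an assumed SD. The bias rests entirely on assumed inputs and runs from negligible to about the size of that half-width, in either direction. For EQ-5D change the concern arises only if a reader or author compares the by-group means. The change is worth making because it is cheap and prevents a causal reading that the design cannot support.

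**What to change.** 1. Keep the crude group means for costs and QALYs as description.
2. As the main exploratory contrast, report a cost difference (bootstrapped) and a QALY difference, each adjusted for a short list of recorded baseline variables fixed in advance, such as age (if it is on the demographic form) and site.
3. Show a further model that adds injury type and surgical or non-surgical treatment, and state that these may lie on the path from IPV to outcome.
4. Replace QALYs lost with difference in QALYs between groups, marked adjusted or unadjusted as applicable, and mark the cost difference in the same way.
5. If EQ-5D changes from baseline are to be compared between groups, add weeks from injury to baseline as a covariate in that comparison.

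Cost: no new data if age is on the form, and a little more analysis. Age takes one degree of freedom. Site takes four with the five sites of Sample size determination, or five with the six named under Study location and clinical sites. That is 5 or 6 parameters for about 225 women, of whom about 75 are exposed. If even this is not wanted, the wording change in step 4 costs nothing and removes the causal label.
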